### Body composition

Dual-energy X-ray absorptiometry (DXA) (Lunar Prodigy 2000, General Electric, Madison, WI, USA) will be used to determine body composition, including lean mass, percentage fat, bone mineral density (BMD) and bone mineral content (BMC). DXA is a safe, standardized instrument to measure bone density both in clinical settings and for research purposes [60]. A calibration check of the DXA machine will be performed on the day prior to starting measurements. We will perform two scans on each participant: total body and lumbar spine, that are recommended by the International Society for Clinical Densitometry, as the most accurate and reproducible sites in children to assess the BMD [60]. Total body, leg and trunk lean mass, and total fat mass will be derived from the total body DXA scan. The BMD and BMC of total body less head (TBLH) and lumbar spine (L1-L4) results will be presented and analyzed in real values (derived from the machine) and height-adjusted values (uses Lunar international reference database [61]). The necessity of presenting height-adjusted values in the pediatric population has been widely discussed and recognized as appropriate given the impact of short/ tall stature on the densitometry results.

### Physical activity

An activPAL™ accelerometer (PAL Technologies Ltd., Glasgow, UK) will be used to assess participants’ free-living physical activity over 5 consecutive days following their assessment [62]. A 5-day monitoring period was chosen following Ishikawa et al.’s (2013) recommendations, who validated activPAL™ as a reliable measurement tool for children with CP GMFCS levels I–III age 2–14 years old [63]. ActivPAL™ will be attached to the mid-thigh of the dominant leg using a waterproofed dressing. A member of the research team will follow up with families via phone or email in 2 days (36–48 h) after the assessment visit to ensure there are no concerns or issues with the device being used. The average number of steps per day, as well as time of sitting/lying/stepping activities, will be analysed.

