### Secondary outcomes

The secondary outcomes include body composition, muscle power, physical activity level, balance, gross motor function, respiratory function, and quality of life. All the outcomes will be assessed four times over the study period: baseline, at 12, 24, and 32 weeks (Fig. 1b).

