### Clinical assessments/data collection

All participants will have four assessment visits at the Maurice and Agnes Paykel Clinical Research Unit (Liggins Institute, The University of Auckland) (Fig. 1b): 1 – baseline (T0), 2–12 weeks after the lead-in period (control) (T1), 3 – after 12 weeks of vibration therapy (T2), 4 – after completing 20 weeks of vibration therapy (T3). During the first visit, written informed consent will be obtained from a participant’s parent/guardian and, if possible, a child assent form from participants older than 7 years old. Information on demographic, ethnicity, medical history (including the history of birth, comorbidities, previous surgery, Botox injections, injuries, and admissions to the hospital) and medications currently taken will be recorded. We also will collect information on the frequency and duration of activities children undergo at school (e.g., physical education classes) and out of school (e.g., swimming, horse riding, walking with a dog, etc.). The procedures will be similar for all four visits and will also include anthropometric measurements, resting blood pressure and heart rate, mobility, body composition, muscle function, physical activity, gross motor function and respiratory function assessments, and the quality-of-life questionnaire.

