#### Data analyses

The data will be entered into an Excel workbook on password-protected computers, and later exported into SPSS v25 (IBM Corp, Armonk, NY, USA) and SAS v9.4 (SAS Institute, Cary, NC, USA) for statistical analyses. Baseline demographic and clinical characteristics of participants will be summarised by trial group allocation. Treatment evaluation of the primary outcome (i.e. mobility or distance covered during the 6-min walk test) will be performed on the principle of intention to treat, using data collected from all randomised participants. Data will be analysed using random effects mixed models with repeated measures, to account for the non-independence of measurements on the same participant. Models will incorporate as fixed effects the trial group allocation (20 vs 25 Hz), time-point (assessment II, III, or IV), and their interactions as fixed effects, as well as the participant’s GMFCS level; in addition, the baseline value of the outcome variable will be included as a covariate. There will be no imputation of missing data, as based on our previous studies, we expect very limited or no loss to follow-up. Nonetheless, for a small subset of secondary outcomes, such as certain functional tests on the Leonardo platform that cannot be performed by participants with GMFCS level III, only subgroup analyses will be carried out including solely participants with GMFCS level I-II. Model-adjusted differences between randomization groups and within groups (including the potential effects of treatment duration) will be calculated and reported with 95% confidence intervals. All statistical tests will be two-sided at *p* < 0.05, without adjustments for multiple comparisons.

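### Activity is averaged over whichever 5 days follow each visit, with no day-type term, so the mix of school, weekend and holiday days can differ between a child's visits

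*Protocol article*

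**What the plan says.** The Physical activity section measures "free-living physical activity over 5 consecutive days following their assessment". The summary is then fixed: "The average number of steps per day, as well as time of sitting/lying/stepping activities, will be analysed". The length of the window rests on a cited validation study in children with cerebral palsy ("A 5-day monitoring period was chosen following"). The section gives no rule for the weekday of the visit, for the number of school and weekend days, or for term and holiday.

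The Secondary outcomes section sets the timing: "All the outcomes will be assessed four times over the study period: baseline, at 12, 24, and 32 weeks". Under Data analyses, the mixed model contains randomised group, "time-point (assessment II, III, or IV), and their interactions as fixed effects, as well as the participant’s GMFCS level", and the baseline value. It lists no term for day type or school term. The planned contrasts are of two kinds: "Model-adjusted differences between randomization groups and within groups (including the potential effects of treatment duration) will be calculated".

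The Clinical assessments/data collection section shows that the school setting was in mind ("We also will collect information on the frequency and duration of activities children undergo at school"), but no use of that information in the activity analysis is stated.

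**The concern.** A child's activity on a school day may differ from that on a weekend or holiday day. A 5-day window must over- or under-represent weekends relative to a 7-day week, and it may fall wholly inside a school holiday. If the mix differs between two visits of the same child, the difference enters the change in average steps with no change in behaviour.

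This design is more exposed than most. Every child has 12 weeks of usual care and then 20 weeks of therapy, in that fixed order. The evidence on therapy itself, and on 12 versus 20 weeks, is therefore change within children over calendar time. Own-control comparison removes stable differences between children but not anything that varies with the calendar. Randomisation protects only the comparison of the two frequencies. Training may also take place at school, so some schedules may follow school terms; that is an inference, not something the protocol states.

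**Working it through.** The plan gives no figure for this outcome that could be reproduced, so the check is a count followed by a range.

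**Inputs.** From the protocol: 5 consecutive days after each visit; visits at weeks 0, 12, 24 and 32; 24 children per group. Assumed, because the document gives no figure:
- visits fall on Monday to Friday;
- wear counts from the day after the visit;
- school and non-school days differ by 1,000 to 3,000 steps, or, on a relative scale, non-school days have a fraction r = 0.10 to 0.40 fewer steps (the sign could be reversed);
- holiday days resemble weekend days.

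**Step 1: weekday under the nominal schedule.** 12 × 7 = 84, 24 × 7 = 168 and 32 × 7 = 224 days, all multiples of 7. A child seen exactly on schedule returns on the same weekday, and the weekend count does not change. The protocol does not require the same weekday.

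**Step 2: weekend days per window.** A Monday visit gives Tuesday to Saturday, which holds 1 weekend day. Visits on Tuesday to Friday each give 2. Two visits therefore differ by at most 1 weekend day. If weekdays were random, the count would differ in 2 × (1/5) × (4/5) = 32% of pairs.

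**Step 3: size of a one-day difference.** Absolute: (1/5) × 1,000 to 3,000 = 200 to 600 steps/day. Relative: with w weekend days the mean, as a multiple of the school-day level, is 1 − r·w/5.
- Going from 1 to 2 weekend days at r = 0.10: 0.96/0.98 − 1 = −2.0%.
- The same at r = 0.40: 0.84/0.92 − 1 = −8.7%.
- In the other direction: +2.1% and +9.5%.

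**Step 4: noise or bias from weekday drift.** With random weekdays the mean apparent change is about zero (at most 0.13% over this range). Its SD per child is 1.17 to 5.16 percentage points, so the standard error for a group of 24 is 1.17/√24 = 0.24 to 5.16/√24 = 1.05 percentage points. This is noise.

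**Step 5: a holiday window.** A term-time window holds 3 or 4 school days, and a window wholly in the holidays holds none.
- Absolute shift: (3/5) × 1,000 = 600 up to (4/5) × 3,000 = 2,400 steps/day.
- Relative shift: (1 − r)/(1 − r·w/5) − 1. The smallest is at r = 0.10, w = 2: 0.90/0.96 − 1 = about −6%. The largest is at r = 0.40, w = 1: 0.60/0.92 − 1 = about −35%.

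Whole-week spacing does not remove this shift. It moves a group mean in proportion to the share of children affected. If a quarter had holiday windows at one visit and none at another (illustrative), the mean would move by 0.25 × 600 to 0.25 × 2,400 = 150 to 600 steps/day.

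**The case against.** The best defence is that the article does not say the average is unweighted, and that day weighting is the kind of accelerometer detail a full protocol or analysis plan may hold. That lowers the weight of the point but does not remove it. The article does fix the window, the summary and the model terms, and followed as written they let the day mix into the contrasts. The cited basis for 5 days does not settle it either: what that source says about day types cannot be seen here.

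Three stronger readings are tempting, and the document does not support them.
- **That the mix does change between visits.** On the nominal schedule the weekday stays the same. A change needs departures from schedule or a change between term and holiday. Both are possible; neither is shown.
- **That the swing is from no weekend days to two**, or 400 to 1,200 steps/day on the same assumption. This needs a window that starts on the visit day with one visit on a Monday, or a Sunday visit. The protocol places the days after the assessment, and on the next-day reading the weekday-visit swing is one day.
- **That night sleep within sitting/lying time creates a false change.** The waterproofed dressing suggests continuous wear, but this is not stated. Five days hold about five nights at every visit, so sleep would dilute the measure, and nothing shows that it would shift between visits.

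The defence is also right that weekday drift is mainly zero-mean noise.

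**Conclusion.** The point holds in a limited form. The activity outcome is exposed to the calendar, and neither the window nor the model guards against it. Weekday drift adds modest noise: at most 200 to 600 steps/day in one child's change on a next-day start. Alignment of visits with school holidays is the larger risk. It could shift a child's mean by 600 to 2,400 steps/day and would bias the control-versus-therapy and 12- versus 20-week contrasts. The comparison of 20 with 25 Hz is not expected to be biased.

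All step figures rest on an assumed difference between day types of 1,000 to 3,000 steps, and the holiday figures also on holidays resembling weekends. Whether visits will in fact cluster in holidays cannot be known from the protocol. As activity is one of several secondary outcomes, this is a refinement and does not touch the primary analysis.

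**What to change.** Label each monitored day from its date as school day, weekend or holiday. Analyse daily values in the planned mixed model, with group, time-point, their interaction, GMFCS level, baseline value and day type as fixed effects, and child and visit-within-child as random effects. Put the baseline value on the same day-type basis, since it comes from a 5-day window too. Treat sitting/lying and stepping time in the same way.

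A simpler alternative is (5 × school-day mean + 2 × weekend-day mean)/7 for each visit where both day types are present. In term time this holds for every Monday-to-Friday visit with a next-day start. It removes the weekend part but not the holiday part.

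The cost is some programming and use of the school calendar; nothing changes for families. The downside is that a window lacking a day type gives a model-based value, not an observed one. If nearly all windows at one time-point fell in holidays, adjustment could not cleanly separate holiday from time-point, so the day-type counts should be tabulated by visit. State the rule before the activity data are examined.

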### Quality-of-life evaluation

Parents/caregivers will be asked to complete the Cerebral Palsy Quality of Life Questionnaire for Primary Caregiver (CP QOL) to evaluate child social and school well-being, feelings about functioning, pain and impact of disability, general well-being and participation, communication and physical health as well as family health (66 items in total). The questionnaire has shown strong psychometric properties [64] and is widely used for research purposes [16, 65]. To avoid the different perception of the child’s well-being by parents/caregivers, the same person will be asked to fill the questionnaire throughout the duration of the study. The total score and score for each domain will be calculated and analyzed.

### Data collection and management

All data collected will remain confidential. Each participant will be entitled with a unique code and all data and information will be subsequently coded. Only researches will be able to match code with a subject. All collected data and information will be stored in locked cabinets and in a secure computer database which will be accessed only by the study investigators with a password.

Data will be stored in common data formats (.pdf, .txt, .csv) on a secure server for a minimum of 10 years. Hard copies of all assessments and personal information will be stored in a locked cabinet at the Liggins Institute. Scientific data will be used in scientific publications, presentations, and the student PhD thesis. No person will be identifiable from the analysis and publications.

### Safety monitoring process

To monitor safety, the study’s internal safety monitoring committee has been created. The committee will have meetings on a quarterly basis. In case of a serious adverse event(s), the committee will have meetings more frequently. Continued communication with patients/families during the intervention period will assist in identifying adverse events. Participants and their families will be asked to record and immediately report any adverse events that may be associated with VT, including tiredness or pain. All adverse events will be reported to and discussed by the safety monitoring committee.

Vibration therapy will be discontinued in any participant who experiences excessive or persistent pain/aching; experiences bone fractures or any illness that would preclude training. The study will be terminated by the committee if two serious adverse events of the same nature will be registered.

### Statistical considerations

#### Sample size

The sample size calculation was performed in GPower software version 3.1.9.2. For the calculation, we used the mean and standard deviation obtained in the 6MWT from the clinical trial performed of 40 participants with cerebral palsy [14]. Setting the level of statistical significance at 0.05 and power at 0.95, a minimum size of 44 participants for two groups was found. Considering a 10% drop-out rate, the final sample will include 48 participants in total, with 24 for each intervention group.

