Vibration therapy (VT) was introduced about 20 years ago as a prospective rehabilitation approach for children and adults with CP. VT is well tolerated by children with CP with no serious adverse effects reported [14–18]. The most frequently described side effects include temporary redness and itchiness of the leg skin that has an adaptive effect [17, 19, 20]. To date, only one study has reported fatigue and pain as a reason of discontinuation single vibration sessions in fewer than 1% of training sessions with no evidence that these effects had been caused by vibration training [21]. VT has been found to be an effective and cost-efficient method to improve muscle strength [15, 17], decrease spasticity [17] and, consequently, improve mobility [16, 17, 21] in this population. In addition, previous studies have reported VT to be effective in improving muscle function [16, 17, 22], bone mineral density [16, 22, 23], gross motor function [17, 22], as well as the quality of life [16] in children and young adults population. A recent review by Ritzmann et al. (2018) that appraised 28 published studies on the effects of VT on functional, neuromuscular and structural parameters of patients with CP revealed an emerging collective evidence that speaks to the potential of VT in ameliorating the symptoms of the disease in both short term (i.e., reducing reflex excitability, spasticity, and coordination deficits) and long term (i.e., improving movement ability, increasing muscle mass and bone mineral density) [24]. However, despite the promising results demonstrated by VT, its wider application is limited by the heterogeneity of methodological approaches used in extant research, with protocols varying in frequency and duration, which complicates the interpretation of the results and the development of treatment protocols [15, 17, 21–23, 25, 26]. In the reported longitudinal studies, the duration of the vibration training varied from 3 to 24 weeks and the target frequency of the vibration stimuli ranged from 18 to 25 Hz [24]. To our knowledge, there have been no published studies that compared the effect of different duration and frequency parameters of side-alternating vibration therapy on the health outcomes of children with CP in longitudinal studies. Therefore, it is still unclear whether higher intensities and/ or longer interventions will bring more health benefits or not. As summarized in the aforementioned systematic review of extant research on the effectiveness of VT, “while the success of VT has been outlined clearly … systematic judgment on the choice of VT parameters requires further investigation” ([24], p. 1623).

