The main limitation of the study is the lack of a control group. We decided to utilize a study design where each participant acts as their own control for a number of reasons. Foremost, children with CP present a heterogeneous population with a variety of symptoms, which makes randomization with control and intervention groups problematic [66] and using each child as their own control adjusts for these issues. In this study, each participant serves as his/her own control, with the control period followed by an intervention period. This design has additional advantages. First, it eliminates the variability on the VT response due to participants’ individual characteristics because the statistical analysis is based on the within-subject comparison. Second, it is suitable for the CP population as their symptoms tend to be stable over time [1].

Another anticipated limitation of the study is that the number of the participants who have completed intended assessments may be uneven due to some subjects’ inability to perform some tests (e.g., S2LJT, chair rising test). However, we do not expect this to be a serious limitation, because, according to the eligibility criteria, children with a high level of disability will not be enrolled in the study.

In summary, the proposed study will expand the knowledge on the efficacy and effectiveness of side-alternating VT in children ages 5 to 12 years with mild to moderate CP. It will help understand the benefits and applicability of vibration therapy to improve the muscle and bone health, mobility, and other health aspects. As a result, the study will assist in defining more robust guidelines for the use of vibration therapy in young children with CP and will provide actionable insights to physiotherapists, families and the affected individuals into the optimal ways to use this therapeutic approach.

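### The stated 0.95 power reads as belonging to the randomised 20 vs 25 Hz comparison, but the documents do not support it for that contrast, and 48 children do not quite cover a 10% loss

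*Protocol article*

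**What the plan says.** The Sample size section names G*Power as the software and describes its inputs only as follows: "we used the mean and standard deviation obtained in the 6MWT from the clinical trial performed of 40 participants with cerebral palsy". The result is given as "Setting the level of statistical significance at 0.05 and power at 0.95, a minimum size of 44 participants for two groups was found". The allowance for loss follows: "Considering a 10% drop-out rate, the final sample will include 48 participants in total", split as 24 per intervention group. The article prints no target difference, SD, test or sidedness in that section.

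Four other places bear on it:
- Study design and Randomization: the only two intervention groups are 20 Hz and 25 Hz.
- Background: to the authors' knowledge, "there have been no published studies that compared the effect of different duration and frequency parameters of side-alternating vibration therapy" in longitudinal studies of children with CP. The Discussion repeats that frequencies had not been compared in this population.
- Data analyses: a repeated-measures mixed model with group, time-point (assessments II to IV), their interaction and GMFCS level, with the baseline value as a covariate. It reports differences both between and within groups, and "All statistical tests will be two-sided at" the 5% level.
- Discussion: in defending the own-control design, the article says that "the statistical analysis is based on the within-subject comparison".

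**The concern.** The wording about two groups, followed by 24 for each intervention group, attaches the 0.95 to the randomised comparison. Yet by the article's own account there was no earlier frequency comparison from which an expected 20 vs 25 Hz difference could be taken. What an earlier trial of this therapy could supply directly is an SD or a before-after change. The Discussion's within-subject description points the same way, while the analysis model addresses both contrasts. The reader cannot tell which one was powered.

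The trial aims to help define the best frequency and duration. If a null frequency result is reported against a stated 95% power, readers may conclude that 20 and 25 Hz work equally well. Whether the trial can bear that conclusion depends on how small a difference it can detect.

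**Working it through.** **Inputs from the documents.** Alpha 0.05, two-sided (sidedness from Data analyses); power 0.95; total 44, so 22 per group at equal allocation; 48 enrolled; loss 10%. **Assumed, not in the documents:** the correlation r between baseline and follow-up 6MWT, shown over a range.

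**1. The plan's own figure.** The 44 cannot be recomputed forward, because the article prints no effect size or test. It can only be solved backwards for the effect it implies.

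**2. Unadjusted two-group reading.** Two-sample t test, df = 42, noncentrality = d × √(22 × 22/44) = d × √11. Setting power to 0.95 gives d = 1.11. (Normal approximation: (1.960 + 1.645) × √(2/22) = 1.09.) A one-sided test would still need 1.01.

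Power with 22 per group, unadjusted:

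| True difference (SD) | 0.3 | 0.5 | 0.8 | 1.0 |
|---|---|---|---|---|
| Power | 16% | 37% | 74% | 90% |

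**3. With the planned baseline covariate.** The residual SD is multiplied by √(1 − r²), so the detectable difference in raw 6MWT SDs is 1.113 × √(1 − r²):

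| Assumed r | √(1 − r²) | Detectable at 0.95 power | Power at 0.5 SD |
|---|---|---|---|
| 0.5 | 0.866 | 0.96 SD | 47% |
| 0.6 | 0.800 | 0.89 SD | 53% |
| 0.8 | 0.600 | 0.67 SD | 77% |
| 0.9 | 0.436 | 0.49 SD | 96% |

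The detectable difference falls below one raw SD once r exceeds √(1 − 1/1.113²) = 0.44. At r = 0.8, a difference of 0.3 SD becomes 0.3/0.6 = 0.5 residual SD and has 37% power.

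**4. Before-after reading.** A paired t test on 44 children (df = 43, noncentrality = dz × √44) reaches 0.95 power at dz = 0.56. That describes the average change across all children and gives no power for 20 vs 25 Hz. For illustration, suppose the average gain in one group were 0.56 SD of change. Comparing changes, 22 vs 22, power would be 44% if the other frequency gave no gain (difference 0.56) and 15% if it gave half the gain (difference 0.28).

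**5. Group-by-time reading.** A repeated-measures interaction test with 2 groups, 3 visits, correlation 0.5 and f = 0.25 also returns 44. For group differences of (0, δ, δ) over the three visits, f = (δ/2) × √(2/9) = 0.236δ, so f = 0.25 means δ = 1.06 SD. All these settings are guesses. At N = 44 the required f scales with √(1 − correlation), so δ would be 1.06 × √(0.2/0.5) = 0.67 SD at a correlation of 0.8 and 1.06 × √(0.1/0.5) = 0.47 SD at 0.9. The match shows that 44 is attainable this way, not that it was obtained this way.

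**6. Loss allowance.** 44/0.9 = 48.9, so 49 are needed (50 for equal groups). 48 × 0.9 = 43.2, so about 43 complete. 48 covers a loss of 1 − 44/48 = 8.3%. At d = 1.11, power with 22 + 21 children is 0.945 and not 0.950.

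**The case against.** A reader might infer that the 0.95 cannot belong to the frequency comparison at all. The documents do not show that. A t test at d = 1.11 gives 44, as does an interaction test at f = 0.25, and if either was used the 0.95 is formally correct for that effect. An SD from an earlier trial can also be paired with a chosen target difference, so having no earlier frequency comparison does not invalidate a calculation. It does mean that the only effect source the article names cannot have supplied this contrast, and no chosen target is given in its place.

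A reader might also infer that the trial can detect only differences above one SD. That is the unadjusted figure. The planned model uses the baseline value, and with a moderate to high correlation the detectable difference is smaller, so this objection stands in full.

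A journal article may leave the effect size and test to a fuller document, and their absence alone is not a fault. The point here is narrower: a power figure is stated in words that tie it to the two intervention groups, and what the article says elsewhere does not support that tie.

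The loss shortfall is small. 44 × 1.1 = 48.4 rounds to 48, the cost is about half a percentage point of power, and Data analyses expects little or no loss. It is a correction to a figure and carries no weight beyond that.

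Finally, nothing in the article says that a null result will be read as equivalence, and Data analyses already commits to 95% confidence intervals. That limits the harm, but a stated 95% power still invites the misreading.

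**Conclusion.** The point holds in limited form and should be fixed. As written, 0.95 reads as the power for 20 vs 25 Hz, and the documents do not support it for that contrast. Unadjusted, it corresponds to about 1.11 SD. Under the planned baseline adjustment it corresponds to 0.96 down to 0.49 SD for assumed correlations of 0.5 to 0.9. At r = 0.9 a 0.5 SD difference would be well covered; at 0.8 or below, moderate and small differences would not reach the stated power.

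The adjusted figures treat the comparison as one at a single follow-up, rest on correlations that the article does not give, and leave aside any further gain from GMFCS level or from combining visits. The separate finding on loss rests on the article's own numbers alone: 48 less 10% is one child short of the stated minimum of 44.

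**What to change.** Keep 48 children and rewrite the Sample size paragraph:

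1. Name the contrast, test and effect size that the 44 and 0.95 refer to.
2. Do not present 0.95 as the power for 20 vs 25 Hz unless a target difference of the matching size is stated and justified.
3. Give the detectable 20 vs 25 Hz difference, in SD and in metres, for 22 per group under the planned baseline-adjusted model, over a range of baseline correlations.
4. State that a non-significant frequency difference will be read from its 95% confidence interval and not as evidence of equivalence.
5. Restate the loss allowance as about 8%, or the expected completers at 10% loss as 43.

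The cost is one rewritten paragraph and probably a less favourable power statement for the frequency comparison. Recruitment, conduct and the analysis model do not change.
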